#### 4.1.4. Asthma medication

Preventer and reliever medication are commonly prescribed to children for wheeze and asthma. Whereas relievers are prescribed in acute phases, to relieve acute symptoms, preventers are prescribed for more severe asthma, to decrease inflammation and prevent episodes.

In the five-year questionnaire, if the parent/guardian indicated that the child had either asthma or wheezing, the parent/guardian was asked whether the child had ever used any medication, pills, puffers or other medicines for wheezing or asthma. If yes, they were presented a list of medications that included:

##### Relievers

Salbutamol (e.g Ventolin, Asmol)  
Pulmicort (Budesonide)  
Prednisolone (e.g Redipred, PredMix, Predsol)  
Atrovent (Ipratropium Bromide)

##### Preventers

Flixotide (Fluticasone Propionate)  
Seretide (e.g Fluticasone and Salmeterol)  
Alvesco (Ciclesonide)  
Singulair (Montelukast)  
Symbicort (Formoterol)

If they selected any of the medications, they were then asked if the child had used it in the last 12 months.

Any 'other' medications listed will be classified as a preventer or reliever as appropriate.

## 4.2. PRIMARY OUTCOME

### 1. Asthma ever, defined by ISAAC questions

**Positive** if the parent/guardian answered 'yes' to 'Has your child ever had asthma?' (ISAAC Q6).

**Negative** if the parent/guardian answered

- 'no' to 'Has your child ever had asthma' in the 5-year questionnaire (ISAAC Q6).
- OR
- 'no' to the asthma question in the 7 – 10-year follow-up questionnaire

**Missing** if in the 5-year questionnaire the response to ISAAC Q6 is missing or don't know AND the response to the follow-up questionnaire is not 'no'.

#### 4.3. SECONDARY OUTCOMES

##### 1. Current asthma at five years of age, defined by ISAAC questions

**Positive** if in the 5-year questionnaire the parent/guardian answered 'yes' to 'Has your child ever had wheezing or whistling in the chest in the chest at any time in the past?' (ISAAC Q1) AND 'Has your child had wheezing or whistling in the chest in the past 12 months?' (ISAAC Q2) AND 'Has your child ever had asthma?' (ISAAC Q6).

**Negative** if in the 5-year questionnaire the parent/guardian answered:

- 'no' to 'Has your child ever had wheezing or whistling in the chest in the chest at any time in the past?' (ISAAC Q1)

OR

- 'yes' to 'Has your child ever had wheezing or whistling in the chest in the chest at any time in the past?' (ISAAC Q1) AND 'no' to either or both of:
  - 'Has your child had wheezing or whistling in the chest in the past 12 months?' (ISAAC Q2)
  - 'Has your child ever had asthma?' (ISAAC Q6) in the five-year questionnaire.

OR

- 'no' to the asthma question in the follow-up questionnaire

**Missing** if in the 5-year questionnaire responses to the above questions are missing AND the response the follow-up questionnaire is not 'no'

OR

The participant does not fulfil the 'positive' or 'negative' criteria above.

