#### 4.1.2. ISAAC questions at five years of age

At five years of age the questionnaires included validated questions from the International Study of Asthma and Allergies in Childhood (ISAAC).

These questions are:

1. *Has your child ever had wheezing or whistling in the chest at any time in the past?*  
*Yes/No/Don't know*

If they answer yes to the first question, the following question was asked:

2. *Has your child had wheezing or whistling in the chest in the past 12 months?*  
*Yes/No/Don't know*

If they answer yes to this question, the following questions were asked:

3. *How many attacks of wheezing has your child had in the past 12 months?*  
*None | 1 to 3 | 4 to 12 | More than 12*
4. *In the past 12 months, how often, on average, has your child's sleep been disturbed due to wheezing?*  
*Never woken with wheezing | Less than one night per week | One or more nights per week*
5. *In the past 12 months, has wheezing ever been severe enough to limit your child's speech to only one or two words at a time between breaths?*  
*Yes/No*

All participants were asked:

6. *Has your child ever had asthma?*  
*Yes/No/Don't know*
7. *In the past 12 months, has your child's chest sounded wheezy during or after exercise?*  
*Yes/No*
8. *In the past 12 months, has your child had a dry cough at night, apart from a cough associated with a cold or chest infection?*  
*Yes/No*

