### **5.4. SECONDARY DATA ANALYSES**

For each secondary outcome, the percentage of study participants with the outcome will be presented separately for children in the treatment and non-treatment groups. Comparison between the treatment arms will be estimated using binary regression adjusted for the randomisation stratification factor of birth mode. Results will be presented as adjusted risk difference and its 95% confidence interval (CI).

Intention to treat analysis with multiple imputation will be used for all the secondary outcomes.

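### Current asthma: a five-year 'no' to ever having asthma is classed Missing and imputed when ISAAC Q1 is unknown, although that answer already rules the outcome out

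*SAP*

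**What the plan says.** SAP section 4.3, item 1 (current asthma):

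- **Positive** needs 'yes' to Q1 (wheeze ever), Q2 (wheeze in the past 12 months) and Q6 (asthma ever). The last two conditions read "ISAAC Q2) AND 'Has your child ever had asthma?' (ISAAC Q6".
- **Negative** has three routes. The first is 'no' to Q1. The second is a 'yes' to Q1 combined with a 'no' to Q2, to Q6 or to both: "at any time in the past?' (ISAAC Q1) AND 'no' to either or both of". The third is "no' to the asthma question in the follow-up questionnaire", which needs no five-year answer.
- **Missing** ends with a catch-all: "The participant does not fulfil the 'positive' or 'negative' criteria above".

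Section 4.1.2 gives the response options for Q1 as "Yes/No/Don't know". Q2 depends on Q1: "If they answer yes to the first question, the following question was asked". Q6 does not, because it stands under "All participants were asked".

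Section 4.2 (primary outcome) takes a five-year 'no' to Q6 as Negative for asthma ever, with no condition on Q1. Section 5.4 states that "multiple imputation will be used for all the secondary outcomes". Section 5.2.3 describes imputation by chained equations with 50 completed data sets. It includes the primary outcome in the imputation model and states no logical constraint between outcomes.

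**The concern.** Because Positive requires a 'yes' to Q6, a parent who answers 'no' to Q6 at five years has settled the child's status: current asthma is not possible under the SAP's own definition. The Negative rule uses that answer only if Q1 is 'yes'. If the parent ticked 'don't know' for Q1 or left it blank, the child meets neither rule and the catch-all makes the outcome Missing.

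Two inconsistencies follow. The same child is Negative for asthma ever but of unknown status for current asthma, an outcome that requires asthma ever. And a 'no' given at 7 to 10 years is enough alone, while the same 'no' given at five, the age the outcome concerns, is not.

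At stake is a known negative being replaced by a random draw. Some draws could be positive, which would add false cases and create the impossible combination of current asthma without asthma ever.

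**Working it through.** **Step 1: can the pattern occur?** Yes. Section 4.1.2 lets Q1 be 'don't know', in which case Q2 is not asked, while Q6 is put to everyone. Q1 unknown with Q6 'no' is therefore an ordinary response.

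**Step 2: how do the rules class each pattern?** Let Q1 and Q6 each be yes, no, don't know or missing. Let Q2 take the same four values, but only if Q1 is yes. Let the follow-up be yes, no, unsure or none.

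- Q1 yes: 4 (Q2) × 4 (Q6) × 4 (follow-up) = 64 patterns.
- Q1 not yes: 3 (Q1) × 4 (Q6) × 4 (follow-up) = 48 patterns.
- Total: 64 + 48 = 112.

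The patterns classed Missing although a five-year 'no' makes Positive impossible number 2 (Q1 don't know or missing) × 1 (Q6 no) × 3 (follow-up yes, unsure or none) = 6. The child's status under the two definitions is:

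| Q1 | Q6 | Follow-up | Current asthma (4.3) | Asthma ever (4.2) |
|---|---|---|---|---|
| don't know or missing | no | yes, unsure or none | Missing (6 patterns) | Negative |
| don't know or missing | no | no | Negative (2 patterns) | Negative |

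**Step 3: what does the correction move?** If a five-year 'no' to Q6 alone gives Negative, the 6 patterns become Negative. No other pattern changes class, and no Positive pattern is affected.

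**Step 4: how large could the effect be?** The SAP gives no count of such children and no imputed-positive rate, so both are assumed. Let 0.5% to 5% of the 1,272 randomised children show the pattern, and let 1% to 15% of them be drawn positive.

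- Low end: 1,272 × 0.005 = 6.4 children; 6.4 × 0.01 = 0.06 false cases per completed data set; 0.06/1,272 = 0.005 percentage points on the pooled risk.
- High end: 1,272 × 0.05 = 63.6 children; 63.6 × 0.15 = 9.5 false cases; 9.5/1,272 = 0.75 percentage points.

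**Step 5: what happens to the risk difference?** Suppose a fraction f of non-cases in each arm is affected and a share d of these is drawn positive. A risk p becomes p + (1 − p)fd, and the difference between arms shrinks by the factor 1 − fd. Use the planning risks of section 2.4 (15% and 9.5%) with f = 3% and d = 15%, so fd = 0.0045:

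- Without BCG: 15% + 85% × 0.0045 = 15.38%.
- With BCG: 9.5% + 90.5% × 0.0045 = 9.91%.
- Difference: 5.5 × 0.9955 = 5.475 points, a shift of about 0.025 points.
- Standard error with 635 and 637 children: √(0.15 × 0.85/635 + 0.095 × 0.905/637) = 0.0183, or 1.83 points.
- Shift relative to the standard error: 0.025/1.83, about 1.4%.

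With f = 5%, the shift is 5.5 × 0.0075 = 0.041 points, about 2.3% of a standard error.

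**The case against.** The strongest reply concerns harm. Section 5.2.3 puts the primary outcome in the imputation model. Every affected child is Negative for asthma ever, and no answer pattern is Positive for current asthma while Negative for asthma ever. A model with asthma ever as a predictor would draw positives for these children at a rate near zero. This stands as a limit on size: a draw rate of 10% to 15%, close to the population rate, is an upper scenario and not an estimate. It does not remove the gap. The SAP does not say that this model serves each secondary outcome. Where asthma ever is included, it predicts a negative perfectly, and a fixed rule is safer than relying on how the software copes with that.

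A reader might infer three stronger things that the SAP does not support:

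- **That the treatment effect is materially diluted.** Even the generous assumptions above move it by a few hundredths of a point.
- **That the 7 to 10-year recall overrules the five-year answer.** It cannot overturn a five-year 'no'. Under section 4.1.3 only a follow-up 'no' counts, and the questionnaire went only to children with data missing through incomplete questionnaires. The narrower statement is correct: a later 'no' suffices alone and the five-year 'no' does not. For the same reason the follow-up cannot be relied on to close the gap, since a completed form with 'don't know' may not trigger it.
- **That the primary outcome is affected.** Section 4.2 classes the same child correctly.

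**Conclusion.** The point holds as an error in a derivation rule. On the SAP's wording, a determined negative for current asthma is classed Missing and imputed, which contradicts the treatment of the same answer in section 4.2. The logic needs no assumption.

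The size does. It rests on an assumed frequency of the pattern, an assumed draw rate and an equal share of affected children in both arms. On those terms the effect is probably very small, and close to nil if asthma ever is in the model for this outcome. It is confined to one secondary outcome, and no conclusion of the trial is likely to turn on it. The reason to act is that the rule is wrong and that correcting it before unblinding costs almost nothing.

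**What to change.** Add one limb to the Negative rule in section 4.3, item 1: a 'no' to ISAAC Q6 in the 5-year questionnaire gives Negative regardless of Q1 and Q2, as section 4.2 already does for asthma ever. Leave the other limbs unchanged. Equivalently, state in section 5.4 that current asthma is set to negative before imputation wherever the five-year Q6 is 'no'.

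Nothing more is needed. The follow-up limb should not be reworded for this purpose. Making it conditional on an unknown Q6 would also move children with Q6 'yes', Q1 or Q2 unknown and a follow-up 'no' from Negative to Missing, which is a separate decision. Imputing Q1, Q2 and Q6 individually is a preference. It would require conditional imputation, because Q2 is asked only after a 'yes' to Q1.

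The cost is one sentence in the SAP and a line or two of derivation code. No new data are required. The change should be made before the database is locked and the SAP is finalised.

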##### 2. Current wheeze at five years of age, defined by ISAAC questions

**Positive** if in the 5-year questionnaire the parent/guardian answered 'yes' to both 'Has your child ever had wheezing or whistling in the chest in the chest at any time in the past?' (ISAAC Q1) AND 'Has your child had wheezing or whistling in the chest in the past 12 months?' (ISAAC Q2).

**Negative** if in the 5-year questionnaire the parent/guardian answered:

- 'no' to 'Has your child ever had wheezing or whistling in the chest in the chest at any time in the past?' (ISAAC Q1)

OR

- yes to 'Has your child ever had wheezing or whistling in the chest in the chest at any time in the past?' (ISAAC Q1) AND 'no' to 'Has your child had wheezing or whistling in the chest in the past 12 months?' (ISAAC Q2).

**Missing** if in the 5-year questionnaire responses to the ISAAC Q1, Q2 or Q6 is missing

OR

The participant does not fulfil the 'positive' or 'negative' criteria above.

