##### 3. Asthma severity, defined by ISAAC questions

**Positive** (severe asthma) if the child is positive for the outcome 'current wheeze at five years of age', AND in the 5-year questionnaire the parent/guardian indicated that in the last 12 months the child had:

- 4 or more attacks of wheezing (ISAAC Q3)
- OR
- disturbed sleep one or more nights per week (ISAAC Q4),
- OR
- speech limited to one or two words by wheeze (ISAAC Q5).

**Negative** (mild or no asthma) if the child is:

- negative for the outcome 'current wheeze',
- OR
- positive for the outcome 'current wheeze at five years of age' AND in the 5-year questionnaire the parent/guardian indicated that in the last 12 months the child had
  - 0 – 3 attacks of wheeze (ISAAC Q3),
  - AND
  - disturbed sleep less than once per week (ISAAC Q4)
  - AND
  - no speech limited by wheeze (ISAAC Q5).

**Missing** if the child is missing for the outcome 'current wheeze at five years of age' or ISAAC Q3,4 or 5 and not positive for any other

OR

The participant does not fulfil the 'positive' or 'negative' criteria above.

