#### 4. Asthma severity, defined as use of asthma preventer medication at five years of age

**Positive** (Severe asthma) if in the 5-year questionnaire the parent/guardian reports that the child has used a preventer medication in the last 12 months (with or without use of a reliever medication).

**Negative** (mild or no asthma) if in the 5-year questionnaire

- the parent/guardian reports that the child has not used any preventer medication in the last 12 months
- OR
- responded 'no' to ISAAC Q1 and ISAAC Q6.

**Missing** if the asthma medication section of the 5-year questionnaire was not completed

OR

The participant does not fulfil the 'positive' or 'negative' criteria above.

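### The Missing rules for current wheeze, ISAAC severity and preventer use overlap the Negative rules, because questions skipped by design are not exempted

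*SAP*

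**What the plan says.** SAP section 4.1.2 sets out a branching questionnaire. Q2 (wheeze in the past 12 months) depends on Q1 (wheeze ever): "If they answer yes to the first question, the following question was asked". Q3 to Q5 (attacks, sleep, speech) depend in turn on Q2: "If they answer yes to this question, the following questions were asked". Q6 (asthma ever) is put to everyone. Section 4.1.4 makes the medication questions conditional: they are asked "if the parent/guardian indicated that the child had either asthma or wheezing".

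Section 4.3 gives each secondary outcome a Positive, a Negative and a Missing rule. For the three outcomes at issue, the Missing rule has two arms joined by OR. The second arm is a catch-all for children who meet neither of the other rules. The first arms are:

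- Outcome 2, current wheeze: Missing "if in the 5-year questionnaire responses to the ISAAC Q1, Q2 or Q6 is missing".
- Outcome 3, ISAAC severity: Missing if current wheeze is missing, "or ISAAC Q3,4 or 5 and not positive for any other".
- Outcome 4, preventer use: Missing "if the asthma medication section of the 5-year questionnaire was not completed".

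Section 5.4 applies multiple imputation to all secondary outcomes.

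**The concern.** The Negative rules respect the branching and the first Missing arms do not. A child who was correctly never asked a question has a blank there, and the first arm reads that blank as missing data. The same child then satisfies two mutually exclusive categories, and the SAP does not say which one wins.

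Coding order matters because Missing values are imputed. If the Missing arm were applied as written, current wheeze would be observed only in children who had ever wheezed and severity only in current wheezers. Preventer use would be observed only in children with reported asthma or wheeze. These groups form after randomisation and BCG may affect their membership, so the arms would no longer be compared on a randomised set of observed outcomes. Known negatives would be replaced by model draws, some of them positive.

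**Working it through.** There is no figure in the SAP to reproduce; the check is one of classification logic. The inputs are the branching in sections 4.1.2 and 4.1.4 and the rules in section 4.3, outcomes 2 to 4. Each question was allowed every permitted answer, including 'don't know' where offered and blank. Q3 and Q4 were collapsed at the SAP's own cut-points, and the medication section was coded as preventer, no preventer or blank.

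**Number of permitted patterns**
- Q1 'yes', Q2 'yes': 27 combinations of Q3 to Q5 × 4 for Q6 × 3 for medication = 324.
- Q1 'yes', Q2 'no', 'don't know' or blank: 3 × (4 × 3) = 36.
- Q1 'no', 'don't know' or blank: 3 × (3 + 1 + 1 + 1) = 18, because the medication section opens only if Q6 is 'yes'.
- Total: 324 + 36 + 18 = 378.

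**Where the rules collide**

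| Outcome | Group | Why Negative or Positive | Why also Missing | Patterns in both |
|---|---|---|---|---|
| Current wheeze | Q1 'no' | Negative on Q1 alone | Q2 skipped | 6 of 6 |
| Current wheeze | Q1 and Q2 'yes', Q6 blank | Positive on Q1 and Q2 | Q6 blank | all |
| ISAAC severity | Q1 'no' | Negative for current wheeze | Q3 to Q5 skipped | 6 of 6 |
| ISAAC severity | Q1 'yes', Q2 'no' | Negative for current wheeze | Q3 to Q5 skipped | 12 of 12 |
| Preventer use | Q1 'no' and Q6 'no' | Negative on Q1 and Q6 | medication section never shown | the only Q1/Q6 combination affected |

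For severity, the overlap remains even if current wheeze is first settled as Negative, because blank Q3 to Q5 trigger the Missing arm directly. The only exemption there is for positives.

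For preventer use, a never-wheezer with Q6 'yes' is shown the section and is classified cleanly if it is completed. One with Q6 'don't know' or blank is Missing only, with no conflict.

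**Scale, on an assumption.** For current wheeze, the share of children answering Q1 'yes' or 'no' whom the skipped Q2 would flag is 1 − P(ever wheeze). The SAP gives no ever-wheeze rate. At an assumed 30% the share is 1 − 0.30 = 70%; at an assumed 60% it is 1 − 0.60 = 40%.

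**With only the catch-all arm kept.** Q1 'no' is Negative only, for current wheeze and for severity. Past-only wheezers are Negative only for severity. Q1 'no' with Q6 'no' is Negative only for preventer use. Q1 and Q2 'yes' with Q6 blank is Positive only for current wheeze. Genuine non-response, such as Q1 blank or Q2 blank after Q1 'yes', still meets neither rule and stays Missing.

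**The case against.** The strongest reply is that the harmful reading defeats the SAP's own text. If Missing overrode Negative, the Q1 'no' arm for current wheeze and the Q1-and-Q6 'no' arm for preventer use could never classify anyone. The catch-all arm also points to Missing as a leftover category, and section 4.1.3 uses missing data to mean questionnaires not completed. A careful programmer would probably code Negative first. This stands as a reading of intent, but it does not remove the contradiction. If only the leftover category was meant, the first arm adds nothing but the conflict. The severity rule shows that an exemption was thought necessary and was then written for positives only.

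A reader might go further and infer a specific inflation: with 20% current wheeze and 40% to 60% ever-wheeze, an apparent prevalence of 0.20/0.40 = 50% to 0.20/0.60 = 33%. The documents do not support that. Both inputs are assumed, and the ratio is a complete-case figure. Section 5.2.3 imputes for all randomised children and conditions on asthma ever and, where the model allows, on earlier evidence of asthma. Skipped children would therefore not simply receive the ever-wheezer average.

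A reader might also infer that every never-wheezer is doubly classified for preventer use. Only those with 'no' to Q6 as well are.

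**Conclusion.** The contradiction is real on the SAP's own wording and affects three of the four secondary outcomes. It rests on reading a question skipped by design as a missing response, or as a section not completed; nothing in section 4.3 excludes that for negatives. The listing of Q6 under current wheeze is a separate slip and matters only where Q6 is blank.

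The consequence is conditional. If the first Missing arm is coded as written, a large share of known negatives is imputed, and prevalence and risk differences could be distorted. The size and, for the risk difference, the direction cannot be computed from the SAP. If Negative is coded first, the skip overlaps do no harm. The SAP does not show that the analysis will be wrong, only that two programmers could follow it and obtain different data sets. The primary outcome (section 4.2) is unaffected: its Missing rule tests Q6, which everyone is asked, together with the follow-up answer. Current asthma is outside this point. The matter should be corrected, but it is not critical to the trial's main conclusion.

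**What to change.** For current wheeze, ISAAC severity and preventer use, delete the first arm of the Missing rule and keep only the catch-all: a child is Missing when neither the Positive nor the Negative criteria are met. This takes Q6 out of the current-wheeze rule without further editing.

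Do not add a general rule that skipped questions count as 'no'. It would turn a child with Q1 'no' and Q6 'don't know' into a non-user of preventers, where the SAP now has Missing. It also does not fit Q3 and Q4, which are not yes/no items. It is not needed, since the catch-all alone removes the overlap.

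The cost is SAP wording and derivation code; no new data are required. Section 5.1 requires the SAPs to be final and public before full unblinding, so the rule belongs in the document and should not be left to the programmer.

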##### 3. Asthma severity, defined by ISAAC questions

**Positive** (severe asthma) if the child is positive for the outcome 'current wheeze at five years of age', AND in the 5-year questionnaire the parent/guardian indicated that in the last 12 months the child had:

- 4 or more attacks of wheezing (ISAAC Q3)
- OR
- disturbed sleep one or more nights per week (ISAAC Q4),
- OR
- speech limited to one or two words by wheeze (ISAAC Q5).

**Negative** (mild or no asthma) if the child is:

- negative for the outcome 'current wheeze',
- OR
- positive for the outcome 'current wheeze at five years of age' AND in the 5-year questionnaire the parent/guardian indicated that in the last 12 months the child had
  - 0 – 3 attacks of wheeze (ISAAC Q3),
  - AND
  - disturbed sleep less than once per week (ISAAC Q4)
  - AND
  - no speech limited by wheeze (ISAAC Q5).

**Missing** if the child is missing for the outcome 'current wheeze at five years of age' or ISAAC Q3,4 or 5 and not positive for any other

OR

The participant does not fulfil the 'positive' or 'negative' criteria above.

